#### Secondary outcomes

Mean score of psychosocial questionnaire (Q2) developed by our team, whose dimensions are presented in Table 4Urinary concentrations of: BPA, chlorinated derivatives of BPA, methyl-, ethyl-, propyl-, and butyl-PBConcentration in colostrum of: BPA, methyl-, ethyl-, propyl-, and butyl-PBPercentage of participants who reported consuming PB-free personal care products

**Table 4 Tab4:** Dimensions of the psychosocial questionnaire used in PREVED study

Dimension of the psychosocial questionnaire	Origin of corresponding question or questions	Comment
***Self-esteem***	French version of the “Self-esteem scale” [49]	Score ranges from 10 to 40: the lower the score, the lower self-esteem. Items for this score are self-administered
***Perceived health***	Created for the questionnaire	Score ranges from 0 to 100 on a visual analogic scale
***Health care renunciation and risk aversion***	Inspired by French national investigations [50, 51]	Use of visual analogic scales
***Risk perception***	Created for the questionnaire and based on the Perception of Pregnancy Risk Questionnaire [52]	Use of visual analogic scales. A composite and global score of perinatal risk perception related to EDC exposure was created
***Knowledge about endocrine-disrupting chemicals (EDCs):*** routes and sources of exposure, ability to name some EDC’s molecules or families of molecules and definition of an EDC	Created for the questionnaire	A composite score was created. A catalog of photo images illustrates sources of exposure
***Perceived knowledge about EDCs***	Created for the questionnaire	Use of a visual analogic scale
***Expectations for a “healthy baby”***	Based on “the healthy baby concept” [53]	Use of a visual analogic scale and a catalog of photo images
***Trusted person***	Created for the questionnaire	The answer to this question aims to identify the trusted person, who exerts the most influence on the pregnant woman
***Level of concern about five risks related to pregnancy***	Created for the questionnaire	This exploration is meant to establish a hierarchy, with respect to chemical risk concerns. A catalog of photo images is used
***The way the pregnant woman heard about EDCs and, if so, how she experienced the information she received***	Created for the questionnaire	These two parameters explore the role of information provided by the media, professional studies, and relationships (personal, friendly, professional, health professionals)

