### Sample size

According to the results of the EDDS (Endocrine Disruptors Deux-Sèvres) cohort study, 83% of French women consumed canned food [48]. Thus, we calculated the number of participants based on the primary outcome measure (consumption measure) using a two-sided paired sample *t* test with 0.05 level of significance two-way design and *β* = 0.20. Our hypothesis was that the contextualized intervention would decrease this percentage to 60%, representing a decrease of 23 points, and 58 participants were required for each group. We expected 20% of lost to follow-up participants; consequently, 70 participants are required for each group, out of a total of 210 pregnant women to be included in our study. This number was increased to 273 persons due to significant colostrum loss in an amendment submitted to the Committee for Personal Protection who approved the first protocol (protocol version 10 approved by the Committee for Personal Protection on 15 June 2018).

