### Data collection, management, and analysis

The research nurse performs home visits and collected data at four key moments (Table 5):
Home visit 1: Q1, Q2, and urine analysisHome visit 2: Q1, Q2, and urine analysisChildbirth: childbirth data, urine, and colostrum analysisHome visit 3: Q1 and Q2

Data input is entered by the research nurse and by the study site coordinator on electronic case report forms (e-CRF). Quality control and queries are carried out regularly. Telephone reminders are expected, if necessary, for home visits 2 and 3.

Urine and colostrum samples are collected in glassware provided by the investigator. They are stored at − 80 °C, in polypropylene tubes, in the Biological Resource Centre of the University Hospital of Poitiers (no. BB-0033-00068) for 5 years. These samples are analyzed using reliable ultrasensitive methods previously developed by our research team for BPA and its chlorinated derivatives [54, 55] and new methods for PB developed for this study. All laboratory materials and solvents are tested to ensure that they were free of contamination from target compounds. High-quality compounds and solvents are supplied by reagent manufacturers. Samples are prepared and extracted. Analyte concentrations are determined using Ultra Performance Liquid Chromatography (Shimadzu®, Kyoto, Japan) coupled to an API 6500+ mass spectrometer (ABSciex®, Concord, Canada) equipped with an electrospray ionization (ESI) interface, operating in negative ionization mode. Target analytes are analyzed in multiple-reaction monitoring (MRM) mode using two specific transitions per analyte to ensure the selectivity and the sensitivity of the method. The analytical methods used are validated according to international guidelines [56–59]. These methods allow to detect and quantify trace concentrations of unconjugated forms of BPA, its chlorinated derivatives, and PB. Urinary concentrations of analytes are corrected using urinary creatinine concentrations determined with a Cobas® 8000 (Roche Diagnostics, Mannheim, Germany) and using urinary specific gravity determined with a hand-held refractometer.

Firstly, a descriptive analysis will be performed on sociodemographic data, questionnaire scores, and on EDC concentrations with percentage for qualitative variables and mean, standard deviation, median, maximum, and minimum for quantitative variables.

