Baseline measurements of the three trial arms will be compared using paired *t* tests and *χ*^2^ tests for the analysis of Q1 and EDC concentrations. The results of Q2 in the three groups will be compared by dimension using ANOVA analyses. An intention-to-treat analysis will carried out, and then a per-protocol analysis in aim to take into account population relating to protocol non-adherence.

Main outcome will be compared between home visit 1 and home visit 2. The rest of analysis will be performed between home visit 1, home visit 2, and home visit 3. Multivariate logistic regression will be performed to assess factors influencing main and secondary outcomes.

All statistical analyses will be performed using SAS 9.4® (SAS Institute, Cary, North Carolina, USA).

No interim analyses are scheduled.

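### Logistic regression is the only multivariable model named for all outcomes, but three of the four secondary outcomes are continuous, and urine and colostrum concentrations have no clearly named continuous-scale comparison of arms after baseline

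*Protocol article*

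**What the plan says.** Under Secondary outcomes, the protocol article lists four items: "Mean score of psychosocial questionnaire (Q2) developed by our team", urinary concentrations of BPA, its chlorinated derivatives and four parabens, colostrum concentrations of BPA and the same parabens, and the percentage of women using paraben-free personal care products. The first three are quantities; the last is a proportion.

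The section Data collection, management, and analysis contains four statements that bear on how these are analysed:

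- Description: percentages for qualitative variables and "mean, standard deviation, median, maximum, and minimum for quantitative variables". Scores and concentrations are thus handled as quantitative.
- T tests: "Baseline measurements of the three trial arms will be compared using paired *t* tests and *χ*^2^ tests for the analysis of Q1 and EDC concentrations".
- ANOVA: "The results of Q2 in the three groups will be compared by dimension using ANOVA analyses".
- Regression: "Multivariate logistic regression will be performed to assess factors influencing main and secondary outcomes".

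The section adds that the main outcome is compared between home visits 1 and 2 and everything else across home visits 1, 2 and 3, without naming a test. The Discussion promises adjustment for confounding factors. No linear, mixed or censored regression appears anywhere in the article.

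**The concern.** The regression sentence covers the secondary outcomes without exception, yet ordinary logistic regression models a yes/no response. Applied as written to Q2 scores or concentrations, it would need each of them reduced to two categories. This is a stated method that does not fit the scale of the outcome, which differs from a detail left to a fuller document.

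It matters most for the concentrations. The aim is to reduce prenatal exposure, the main outcome is self-reported in an open-label trial, and the concentrations are the laboratory-measured outcomes. The sample was raised from 210 to 273 because of colostrum loss; reducing colostrum results to two categories would give back part of what that increase bought.

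**Working it through.** **1. What each outcome has, on its own scale, after baseline**

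| Secondary outcome | Scale | Unadjusted comparison of arms | Multivariable model named |
|---|---|---|---|
| Q2 scores | continuous | ANOVA, by dimension | logistic only |
| Urinary concentrations | continuous | none clearly named | logistic only |
| Colostrum concentrations | continuous | none clearly named | logistic only |
| Paraben-free products | yes/no | none clearly named (the χ² sentence is worded for baseline) | logistic, which fits |

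For the concentrations, the t-test sentence begins with baseline measurements. Reading the word paired as a before-and-after test within an arm would keep the continuous scale but would still not compare arms. Colostrum is collected only at childbirth (Table 5 and the list of visits), so neither reading reaches it. The statement that the remaining analyses run across the three home visits names no test and does not include childbirth.

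**2. The plan's own figure**

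The only sample-size figure concerns the main outcome: "83% of French women consumed canned food", and the intervention "would decrease this percentage to 60%, representing a decrease of 23 points, and 58 participants were required for each group", from a "two-sided paired sample *t* test with 0.05 level of significance two-way design and *β* = 0.20". A two-group arcsine calculation for 83% against 60% (two-sided 0.05, power 0.80) gives 58.2; the unpooled formula gives 57 and the pooled formula 60. So 58 reproduces, but it says nothing about the secondary outcomes. Only the significance level and power are carried forward.

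**3. Illustration: what dichotomising would cost**

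Assumptions, none of them in the documents: a normal outcome (after logging, for concentrations), no values below the quantification limit, and two arms compared.

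Relative information after a cut at quantile q, with c = Φ⁻¹(q): ARE = φ(c)² / [q(1 − q)].

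At the median: φ(0)² / 0.25 = (1/2π) / 0.25 = 2/π = 0.637, a loss of 36.3%.

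Power for a comparison that has 80% on the continuous scale: Φ[(1.960 + 0.842) × √ARE − 1.960].

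| Cut at | Information kept | Lost | Power |
|---|---|---|---|
| none | 100% | 0% | 80% |
| median | 63.7% | 36.3% | 60.8% |
| 75th percentile | 53.9% | 46.1% | 53.8% |
| 90th percentile | 34.2% | 65.8% | 37.4% |

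A second method gives nearly the same answer for the median. With d the standardised difference that has 80% power in a two-sample t test, the proportions above the cut are Φ(d/2) and 1 − Φ(d/2), compared by an unpooled z test:

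- 73 per arm (273/3 = 91, less 20%): d = 0.467, power 62.1%.
- 58 per arm: d = 0.525, power 62.5%.

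In effective numbers at a median split, 58 per arm acts like 58 × 0.637 ≈ 37, and 91 per arm like 91 × 0.637 ≈ 58.

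**The case against.** The strongest reply is that the regression sentence is about factors influencing outcomes. It describes a look at determinants and is not presented as the test of the intervention. The same section gives ANOVA for Q2, so that score is compared between groups uncut and loses nothing there. Both points stand. A reader might infer that logistic regression is the only method for the secondary outcomes; the ANOVA sentence contradicts that.

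A reader might also infer that all three continuous outcomes must be cut. The article does not say so: it never uses the word binary, mentions no dichotomising, and an ordinal logistic model would need no single cut-point. That also stands, although no ordinal model is named. The absence of a cut-point is not itself a fault, since the full protocol or analysis plan may contain one.

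Third, the 36% rests on assumptions that the documents neither give nor support with data, and 273 is an enrolment total that exceeds the number of colostrum samples. The figure is therefore an illustration only. Finally, these are secondary outcomes, and the Discussion itself notes that urinary measurements may be unreliable.

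What the reply does not remove is the mismatch. The Discussion promises adjusted results, the only adjusting model named does not suit three of the four secondary outcomes as measured, and for urine and colostrum no other post-baseline comparison of arms is clearly stated.

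**Conclusion.** The point holds as a mismatch between model and outcome scale. Logistic regression is the only multivariable model named, and it does not fit Q2 scores, urinary concentrations or colostrum concentrations unless they are categorised. For Q2 this touches only the adjusted analysis. For urine and colostrum it also leaves the post-baseline comparison of arms on the continuous scale without a clearly named method.

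The size is conditional. For any outcome actually dichotomised, and if it is normal or log-normal, the loss is about 36% of the information at best (median split), with 80% power falling to about 61–62%. It is 46% at an upper-quartile cut and 66% at the 90th percentile. A reader should not take a loss of a third as an established property of this trial, nor apply it to the ANOVA of Q2. The main outcome is yes/no, so this point does not affect it. The wording should be corrected, but the trial's primary conclusion does not depend on it.

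**What to change.** In Data collection, management, and analysis, replace the regression sentence with one that assigns a model by outcome scale:

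- Industrial food and paraben-free products (yes/no): logistic regression, as now.
- Q2 scores: linear regression with arm, the home visit 1 score and the planned factors.
- Urinary concentrations: linear regression of log concentration, or censored regression if values fall below the quantification limit, with arm, baseline log concentration and the planned factors, in a repeated-measures form across the sampling times.
- Colostrum concentrations: the same model without a baseline term.

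Report mean differences for scores and geometric-mean ratios for concentrations, each with a 95% confidence interval. Keeping the planned factors in the models preserves the question about determinants alongside the comparison of arms.

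Before the urine model is written, settle its sampling times: Table 5 marks urine at home visit 3, while the list of visits gives only the two questionnaires there.

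The cost is a few lines of wording, with the same data and the same software. The Data Availability statement says that no data had been analysed when the article was written. If the models are fixed before analysis begins, no cut-point can be chosen after the results are seen.

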### Monitoring

A data monitoring committee was composed by a team from the Research Directorate of University Hospital of Poitiers. It is in charge of auditing trial conduct every 4 months, data management and promoting data quality. It consists of a Clinical Research Associate, a project monitoring manager, a data manager, and also the clinical trials vigilance unit. Consistency tests were performed on e-CRFs. As the study carries no risk, only consent and reporting of serious adverse events are verified.

The only expected adverse event was anxiety. Adverse events are noted at each home visit, throughout the period of participation of pregnant women.

## Discussion

To our knowledge, PREVED is the first study to assess the impact of perinatal environmental health education by promoting the sharing of know-how and experience in a positive and non-alarmist approach. Along with the randomized controlled trial, a sociological approach is applied to analyze the conditions of reach, efficacy, adoption, implementation, and maintenance of the intervention [60]. In particular, observations are carried out during the workshops using grids and describing the interactions between the pregnant women and the workshop animator [61]. Moreover, interviews with stakeholders (researchers, local actors and decision-makers) are conducted to evaluate the transferability of the intervention [62]. The collective and local dynamics underlying the development of intervention and the points of view of participants are thereby assessed [61].

The PREVED study adopted two complementary approaches in the framework of the intervention research process. In fact, intervention research applied to the health field is a specific kind of research that aims to provide information on the impact of interventions on population health using scientific methods [63] and to determine how “to intervene” (not “to discover”) [64]. This design should be well-founded and include partnerships with practitioners [65]. Thus, DisProSE group facilitated partnership with different stakeholders through an interdisciplinary approach.

The PREVED intervention takes on the form of practical 2-h workshops. This configuration is easily reproducible and viable. Indeed, in addition to mention of the effectiveness of intervention research, degree of viability and specification of the mechanisms explaining the effects should be considered in conjunction with “the interventional system” [66].

Furthermore, the main feature of PREVED study is to consider all aspects of lifestyle and to underscore key functions such as sharing of know-how, sharing of experiences and information between participants. In fact, few environmental promotion interventions have shown that EDC exposure was reduced by changing lifestyle. However, previous studies assessed the impact by taking into account only one component of lifestyle, such as nutrition or cosmetics [67, 68] and did not include the dimension of “know-how” [69]. Moreover, these studies took EDC concentrations in urine as their main outcome, even though analysis of the latter may be unreliable [70–72] and did not provide information about psychosocial aspects. This facet will be explored by the psychosocial questionnaire Q2 in our study. Concerning assessment of exposure to EDCs, we chose urine matrix samples because spot samples of urines are not restrictive and ensure optimal acceptability for the pregnant women participating. Twenty-four-hour urine collection may have been preferable, due to non-influence of the time of day. However, spot samples of urines provide reasonably reliable information on impregnation by BPA and PB during pregnancy [73–76].

We made sustained efforts to minimize information bias. Notwithstanding the absence of blindness, the investigator’s practices and behaviors are likely to vary during visits, according to allocation group. That is why hetero administration of questionnaires by a single trained assessor, with a standardized interviewer’s guide, has been adopted. Furthermore, selection bias is controlled by trained PMI nurses wishing to facilitate the enrolment of pregnant women facing difficulties. Enrolment bias is thereby avoided, whereas preceding studies highlighted the fact that participants for this type of study are mostly women with a high socio-economic level [48]. However, in such a cohort, selection bias can still be expected [77] especially for pregnancy cohorts, insofar as women with a high socio-educational level are likely to feel more concerned [78, 79]. We will probably need to determine how to reach populations more effectively in precarious situations. At the time of the analysis, results will be adjusted on confounding factors that affect the psycho-social dimensions and have been highlighted in this study.

## Conclusion

Through this study, we aspire to increase all health stakeholders’ awareness of the importance of primary prevention on exposome, especially EDC exposure, during pregnancy. In fact, given the methodological difficulties in proving EDC’s effects in humans, some authors are convinced that it is impossible to conclusively demonstrate, and they would rather think in terms of prevention actions. That is why research studies should be complemented by interventions designed to reduce EDC exposure, such as primary prevention interventions, notably during pregnancy and other critical windows [28, 80, 81]. This approach also provides the scientific community and decision makers with elements possibly reinforcing their commitment to environmental health promotion.

## Trial status

Since the last recruitment took place in the end of 2019, the last visit will be planned in the end of 2020.

The choice to publish the study protocol after recruitment completion but before the last visit can be justified by the particularity of population health intervention research.

In fact, this kind of study design integrated an “interventional system” as defined by Cambon L et al. as “a set of interrelated human and non-human contextual agents within spatial and temporal boundaries generating mechanistic configurations—mechanisms—which are prerequisites for change in health” [82]. Hence, this “interventional system” required continuous adjustment to the intervention context. That is why theorization of the methodology, and consequently of the protocol, requires more time than a classic therapeutic trial. As a result, we had to step back after the intervention and integrate the dynamism of the interventional system in order to improve the quality of our assessment.

## Data Availability

Paper questionnaires will be automatically anonymized to be entered on e-CRF anonymously and then stored in a locked cupboard. Biological samples will be identified only by the anonymity code. The data sets generated and analyzed during this study are not publicly available. The methodological referent and the doctoral student will have access to the final trial dataset and results will be published in a peer-reviewed journal in 2021 with a defined authorship (Additional file 3). As of now, data have yet to be analyzed.

## Abbreviations

ANOVA: Analysis of variance
BCT: Behavior change techniques
BPA: Bisphenol A
DOHaD: Developmental Origins of Health and Disease
e-CRF: Electronic case report forms
EDC: Endocrine-disrupting chemical
EDDS: Endocrine Disruptors Deux-Sèvres
ESI: Electrospray ionization
FOAD: Fetal Origins of Adult Disease
MRM: Multiple-reaction monitoring
PB: Parabens
PMI: Protection Maternelle et Infantile
POHaD: Paternal Origins of Health and Disease
WHO: World Health Organization
